## **B. Study Type and Design:**

We propose a cluster randomized controlled trial (SA1) enrolling CC screening clients at Kenyan health facilities: n=5 intervention and n=5 matched standard of care (SOC) sites to evaluate the efficacy of the CATSystem to improve guideline-adherent CC screening, treatment, referral and follow-up. SA2 will focus on the feasibility and acceptability of CATSystem implementation, and SA3 assesses the cost-effectiveness of the CATSystem and considerations for scale-up.

**Study Setting:** Kenya has a population of over 50 million people, of whom approximately 59.4% are reproductive age girls/women (15-64yrs). Proposed study sites will be in the Western Kenyan counties of Siaya and Busia where HIV prevalence is among the highest nationally, contributing to increased risk for cervical cancer. Siaya has a population of 993,183 (53% female) and the highest prevalence of HIV in Kenya (21%). Busia has an estimated population of 908,658, (52% female) and the 5th highest HIV prevalence in Kenya at 7.7%. The overall adult literacy rate is 81.5% in Kenya and 75.3% in Siaya and Busia. We have ensured our text messages have a 3 to 5 Flesch-Kincaid grade level. Table 1 details facility level data from the 10 most closely matched study sites from a recent retrospective review of 19 potential hospitals. Priority data points include the number of women: of reproductive age, living with HIV, screened for CC in the past year. We carefully reviewed and described the procedures and capacity for CC screening and treatment at each planned study site to ensure similarity across to optimize matching prior to randomization.

Table 1. Proposed matches from data reviewed October 2021 to September 2022

| Site                          | Busia | Bondo | Port Victoria | Akala | Matayos | Ukwala | Yala | Alupe | Nambale | Khunyangu |
|-------------------------------|-------|-------|---------------|-------|---------|--------|------|-------|---------|-----------|
| Repro aged women in care      | 51551 | 21368 | 8500          | 7060  | 5450    | 7196   | 6236 | 6000  | 5065    | 4156      |
| Women in HIV care (CCC)       | 3306  | 1200  | 591           | 2018  | 370     | 663    | 1271 | 249   | 700     | 1137      |
| Total screen/rescreen         | 4440  | 1878  | 1087          | 1003  | 359     | 477    | 617  | 478   | 730     | 615       |

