| % repro-age women             | 8.6%  | 8.8%  | 12.8%         | 14.2% | 6.6%    | 6.6%   | 9.9% | 8.0%  | 14.4%   | 14.8%     |
| Trained providers (screening) | 10    | 10    | 8             | 6     | 7       | 6      | 3    | 5     | 4       | 3         |

Of 19 sites reviewed, this table shows the best 10 matched sites. All sites have VIA/VILI available for screening and will provide on site treatment with cryotherapy and/or thermocoagulation. Documentation of abnormal screening was variable due to inconsistent documentation. Based on data, we estimate an abnormal screen rate of 1%-5%.

**Study Design:** We propose a matched, cluster randomized controlled study design [2 arms, 5 intervention and 5 control hospitals (clusters), and at least n=30 patients with a positive CC screening result per cluster] to evaluate the efficacy of the CATSystem. The methods for Aims 1-3 are described below.

**Staffing and responsibilities.** We will hire and train one full time lay health worker as a Research Assistant (RA) per study site. Each site RA will be trained to conduct procedures specific to the study arm allocation and know the CC screening and treatment guidelines. Lay health workers have been effective and dependable RAs in prior HITSystem studies and programmatic work as they are already embedded in the facility/community and provide an opportunity to leverage existing relationships and build capacity through a train the trainer model. At all sites, RAs will assess eligibility and conduct informed consent procedures and surveys. At intervention sites, identified clinical staff will be trained on features of the system including how to routinely enter and update patient data, generate required county reports and follow-up with patients as appropriate. RAs will do the majority of data entry in the CATSystem at each participant visit, updating clinical information (services received, lab results, comorbidities, treatment, etc.) per clinician notes. RAs will also lead patient outreach and follow-up efforts (phone or SMS via CATSystem) and coordinate physical tracking, if needed, particularly for diagnoses that require timely treatment. Two Site Coordinators experienced in coordinating research activities on the ground will divide the responsibilities of overseeing activities at the 10 study sites.

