**Sample size considerations.** Assuming average success (treatment completion) rates of 0.10 (SOC arm) and 0.35 (CATS arm), we used R to simulate 5,000 data sets, each with outcome data for five 30-person clusters per arm. A target ICC value for each data set was randomly drawn from a half-normal distribution fit by Turner et al. (2001) to the empirical distribution of 70 ICCs from studies of health outcomes with data clustered within practices, towns, or postal codes. For simulation, each target ICC was converted to a random site intercept variance on the logistic scale using the assumed SOC success rate (0.10) and the Taylor expansion approximation from Turner et al. We simulated success counts for each cluster by drawing a random cluster intercept from a Gaussian distribution with the specified variance, adding the appropriate fixed intercept and (for CATS sites) arm effect on the logistic scale, converting the resulting logit to a probability (p), and taking a random Binomial(30, p) draw. This process reflects our uncertainty in the true ICC. It also produces ICCs larger than the target values because of bias in the Taylor approximation and our use of the SOC success rate to estimate the random intercept variance, which yields a larger ICC among CATS clusters due to their higher success rate. Thus, across the 5,000 data sets, mean ICC was 0.057 for SOC clusters and 0.083 for CATS clusters (vs. mean ICC 0.023 for the half-normal distribution fit by Turner et al.). For a point of comparison, analysis of pilot screening rate data for our ten study sites yielded ICC 0.012.

For each simulated data set we used SAS 9.4 to fit a logistic mixed model with a fixed arm effect and random site intercept. Between-within degrees of freedom were specified as a small-sample adjustment. The mean length of 95% CIs for the arm effect odds ratio was 18.0; power (1-sided test,  $\alpha=0.025$ ) was 86.9%. For comparison, the R package *clusterPower* (<https://CRAN.R-project.org/package=clusterPower>), which has been verified against NIH's GRT Sample Size Calculator and PASS11, yielded power=85.9% for the SOC and CATS rates and ICC=0.05.

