The proportion of screened women with a positive result ranged between 3.4% (53/1576) during the SOC period and 7.1% (39/550) during the intervention period. **To guide enrollment targets, we will assume a positive screen rate of 5%, which would require enrollment of at least n=600 women per cluster to result in 30 women with a positive screen. We will enroll an additional 10% to account for attrition due to relocation, transfer of health facility or death.** During our pilot study, we enrolled 552 patients at the pilot facility over the span of 15 months, however, several months were impacted by Covid-19 restrictions at the health facility (n=3) or a clinical worker strike (n=1) when enrollment numbers dropped from an average of 53 to 24 patients per month. We thus estimate the potential to have enrolled up to 795 patients under more normal conditions. We also anticipate that monthly enrollment numbers may decrease over the 24-month period, given that once a woman has been screened and/or treated, their next screening appointment per guidelines would be within 3 to 5 years; thus fewer women at the health facility will be eligible for screening over the course of the study. With this in mind, **we expect a 24 month enrollment**

**period will be adequate to reach a total of 660 participants at each hospital (660 x 10 sites= 6,600 study participants).**

**Missing data; multiple testing.** Taking an intent-to-treat approach, rather than exclude participants who drop out from analyses we will carry out and compare two analyses, one where dropouts are classified as not receiving treatment, and another where inverse probability of attrition weighting is used to adjust for participants lost to attrition. Missing data on explanatory variables will be imputed using stochastic regression imputation or, if the rate of missing data exceeds 1%, using multiple imputation by chained equations. Consistent with guidance from the statistics community, we will focus on effect sizes and their confidence intervals rather than treating  $p < 0.05$  as a dichotomous indicator of whether an effect is practically important and classifying results as “significant” or “not significant” on this basis. Model selection processes that exploit chance will be avoided.

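### The minimum of 30 positive screens per cluster is only an expected count at a 5% positive rate, the top of the protocol's own 1%-5% estimate for the ten sites, and no power is shown below that rate

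*Protocol*

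**What the plan says.** All references are to the Protocol.

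- **Section II.B, Study Design paragraph:** five hospitals per arm, with a stated minimum of 30 patients with a positive screen per cluster.
- **Section II.B, note under Table 1:** "Based on data, we estimate an abnormal screen rate of 1%-5"%. The sentence before it warns that abnormal screens were inconsistently documented.
- **Section II.C, Sample size considerations:** "Assuming average success (treatment completion) rates of 0.10 (SOC arm) and 0.35 (CATS arm"), with 5,000 simulated data sets, "each with outcome data for five 30-person clusters per arm". Simulated power is 86.9% (one-sided 0.025). A comparison run in clusterPower at ICC 0.05 gives 85.9%.
- **Section II.C, enrolment paragraph:** observed positive rates of 3.4% (53/1576, standard-of-care period) and 7.1% (39/550, intervention period), then "we will assume a positive screen rate of 5%, which would require enrollment of at least n=600 women per cluster". Adding 10% for attrition gives "a total of 660 participants at each hospital".

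**The concern.** The primary outcome is measured only in women with a positive screen, so the number of positives per cluster drives the primary power. Section II.B gives two statements that fit together only at one end of a range: a floor of 30 positives per cluster, and a site-based rate of 1% to 5%. With 600 women, 30 is the expected number at exactly 5%. Any lower rate in the protocol's own range gives fewer.

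Section II.C then adopts 5% without mentioning the 1%-5% estimate, shows no power at a lower rate, and ties enrolment to a number of women and not to a number of positives. A reader would take 86.9% as the power of a design whose cluster size is guaranteed, when that size depends on a favourable assumption. The simulation also draws Binomial(30, p) in every cluster, so neither a shortfall nor unequal cluster sizes enter the stated figure.

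**Working it through.** **Inputs (Sections II.B and II.C).** Rates 0.10 and 0.35; k = 5 clusters per arm; m = 30 positives per cluster; ICC 0.05; one-sided 0.025; 600 women per cluster (660 with the 10% added); positive rates 1%-5%, 3.4% and 7.1%.

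**Step 1: enrolment arithmetic.** 30/0.05 = 600 and 600 × 1.10 = 660, as stated. If all 660 women count, the rate needed for an expected 30 is 30/660 = 4.5%.

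**Step 2: reproduce 85.9%.** Variance of the difference = [0.10×0.90 + 0.35×0.65] × [1 + (m−1)×ICC] / (k×m).

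- 0.0900 + 0.2275 = 0.3175
- Design effect = 1 + 29×0.05 = 2.45
- Variance = 0.3175 × 2.45 / 150 = 0.005186; SE = 0.0720
- Noncentrality = 0.25/0.0720 = 3.47
- Noncentral t with 2(k−1) = 8 df, critical value 2.306: power 85.9%, matching the protocol

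The 86.9% cannot be repeated exactly, because the half-normal parameter and the details of the variance conversion are not given. Mixed-model simulations of the described process with 30 per cluster gave 91%, 84% and 80% as the site variance was scaled by 1, 1.5 and 2, so 86.9% is plausible.

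**Step 3: same formula, only m changed (m = 600 × rate).**

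| Positive rate | Positives per cluster | Design effect | SE | Power |
|---|---|---|---|---|
| 5% | 30 | 2.45 | 0.0720 | 85.9% |
| 4.3% (pooled pilot, 92/2126) | 26 | 2.25 | 0.0741 | 83.9% |
| 3.4% | 20.4 | 1.97 | 0.0783 | 79.8% |
| 3% | 18 | 1.85 | 0.0808 | 77.3% |
| 2% | 12 | 1.55 | 0.0906 | 67.8% |
| 1% | 6 | 1.25 | 0.1150 | 48.1% |

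Power falls below 80% at about 20.7 positives per cluster, a rate of 20.7/600 = 3.45%. If all 660 women count, power is 87.0% at 5%, 81.5% at 3.4%, 79.2% at 3% and 50.8% at 1%.

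**Step 4: different rates by arm.** With 3.4% at control sites (20.4 positives) and 7.1% at intervention sites (42.6):

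- 0.0900 × 1.97/102 + 0.2275 × 3.08/213 = 0.001738 + 0.003290 = 0.005028
- SE 0.0709; power 86.9%

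Control clusters would still average about 20 positives, below the stated minimum.

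**Step 5: is 30 a floor even at 5%?** For X ~ Binomial(600, 0.05), P(X ≥ 30) = 52.6%; with 660 women it is 72.9%. If sites are independent, all ten reach 30 with probability 0.526^10, about 0.2% (about 4% with 660). At 3.4%, a single site reaches 30 with probability 2.5% (6.9% with 660).

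**The case against.** **The 5% has a stated basis.** The sentence before it gives 3.4% and 7.1%, and 5% lies between them. Half the clusters are intervention sites, for which 7.1% is the nearer pilot figure, and the split-rate case loses no power. This stands: 5% is favourable against the site estimate but not invented.

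**The 1%-5% range may be too low.** The protocol says abnormal screens were inconsistently documented. Section II.C also counts women whose result was unreliable because of cervicitis, STI or another comorbidity, and it is not stated whether the 1%-5% includes them. This stands too, and it makes the 1% row an edge case. It does not remove the discrepancy, because the protocol still gives the range as its estimate for these sites.

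**Sites could enrol more.** Twice the annual "Total screen/rescreen" count in Table 1 exceeds 1,000 at seven of the ten sites. The stated target, however, is 660 per hospital, with no rule to continue until a number of positives is reached.

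**Stronger readings the protocol does not support.**

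- A reader might put the simulation's mean ICCs (0.057 and 0.083) into the fixed-ICC formula, obtain about 76%, and conclude that 86.9% is wrong. It does not follow. The simulation already averages over those ICCs, power averaged over a skewed ICC distribution is not power at the mean ICC, and the clusterPower run is offered only as a comparison with its ICC stated.
- A reader might apply the 75.3% literacy figure to the smallest site's volume and conclude that it cannot reach 660. Section II.D does ask for ability to read SMS, but it also allows number codes and says that all women receiving screening will be eligible, so a county literacy rate is not a usable eligibility fraction.

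**Conclusion.** The point holds as a misstatement of the cluster size and an unreconciled planning rate. Thirty positives per cluster is an expected count at 5%, the top of the protocol's site-based range, and not a minimum. The protocol's arithmetic (600, 660, 85.9%) is correct.

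The cost in power is small at the pooled pilot rate (about 2 points), about 6 points at 3.4% and 9 points at 3%. It is severe only at 1% to 2%, and absent if the arms run at 3.4% and 7.1%. A reader might infer that the trial is underpowered, or that 3% is the right planning rate. The protocol supports neither: 3% is only the midpoint of the range and lies below both observed pilot rates.

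These figures rest on the protocol's treatment rates, ICC 0.05, equal cluster sizes within each arm and 600 analysed women per site. The chances of reaching 30 assume independent screens at a common rate; variation in the rate between sites would make counts more unequal.

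**What to change.** 1. In Section II.B, replace the minimum of 30 with an expected 30 at a 5% positive rate. Reconcile the 1%-5% estimate with the 5% in Section II.C: say which data each rests on, whether the site estimate includes results made unreliable by infection, and why 5% is used.
2. In Section II.C, replace the single 86.9%/85.9% with positives per cluster and power at 1%, 3%, 3.4%, 4.3% and 5%. By the formula at ICC 0.05 and 600 women these are 6, 18, 20, 26 and 30 positives, and about 48%, 77%, 80%, 84% and 86%. The split case of 3.4% and 7.1% (about 87%) can be added.
3. Rerun the simulation with site-specific positive counts that vary, in place of a fixed 30, and report that result as the main figure.

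The cost is a rerun of existing code and a somewhat less favourable power statement. No extra participants are needed.

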#### **D. Subject Criteria (See Vulnerable Populations appendix, if applicable):**

**Health Facility Eligibility and Selection.** Eligible sites must provide CCC and MCH/FP services and serve an average at least 4000 reproductive aged women. A repeated assessment of the previous three months will be conducted prior to study start to capture any changes that may require adjustments to the planned sites. All eligible facilities will be yoked in pairs matched on volume of reproductive aged women, average number of women screened per month, and screen and treat capacity. The study statistician will randomly allocate one site in each pair to the intervention.

**Participant Eligibility and Consent.** Eligibility will be restricted to women >16 years of age (age of treatment consent is 16 yrs) with access to a cell phone and ability to read SMS’s at a 3rd-5th grade level. While literacy levels in Bungoma and Busia are high, women can opt to customize SMS messages to include pre-specified familiar greetings or numbers to indicate the need to contact or return to the health facility (e.g. ‘afya’ [Swahili for healthy] or ‘7777’). To maximize generalizability, all women receiving CC screening at CCC or MCH/FP during the study period will be eligible for enrollment. Pregnant women (>20 weeks) who are not eligible for CC screening per Kenyan guidelines, incarcerated patients or women with impaired mental capacity affecting ability for informed consent will be excluded from the study. Women opting out of the study will be offered standard CC screening services without CATSystem enrollment. All participants will be informed of the purpose of the research, including potential benefits and risks, prior to a request for written informed consent. Guardians of eligible girls <18 years of age will be required to sign a written, informed consent and the eligible girl will be asked to provide written assent. Site Research Assistants (trained lay health workers) familiar with CC screening procedures and providers will document study enrollment and enrollment refusal at all sites.

## **E. Specific methods and techniques used throughout the study**

All laboratory tests (i.e. VIA/VILI, HPV testing, PAP for cervical cancer screening) and clinical management (i.e. Cryotherapy, thermocoagulation, LEEP, chemotherapy, radiation for cervical cancer treatment) will be provided by trained clinical providers at the study hospitals, per national guidelines and standard of care procedures. That CATSystem will prompt and support patient retention through these routine clinical services but will not provide additional laboratory diagnostic tests or treatments outside of the standard of care recommendations based on the participant's clinical presentation. All samples will be handled, stored, and destroyed per the hospital's established procedures.

## **F. Risk/benefit assessment:**

1. **Physical risk:** While providers are most experienced with cervical cancer screening and treatment methods, women receiving screening and/or treatment may experience minimal pain and discomfort associated with standard screening and treatment procedures. While this isn't a risk unique to study participation, study staff will work with clinical staff to ensure women are informed about and prepared for the screening and treatment process. Participants in the intervention arm and in the control arm are at equal risk of experiencing this risk. Women will be counseled through the process of screening and treatment, including be given information about what to expect in terms of discomfort. Training on procedures will be reinforced to minimize risk of errors and need for repeat screenings.
2. **Psychological risk:** The risk of psychological and emotional distress exists, particularly for women receiving a positive screen. While this isn't a risk unique to study participation, if this occurs, we will provide assistance through study staff, clinic peer counselors and - as necessary - clinic medical staff. The risk of psychological distress exists equally among women in the intervention and control arms.
3. **Social risk:** Loss of confidentiality and stigma are concerns. In a setting in which a woman may not have disclosed her cervical cancer screening status to her partner, inadvertent disclosure is a concern. Participants could be treated unfairly or discriminated against, or could face problems being accepted by their partner, family or community. This is a greater concern at intervention sites using the CATSystem, as the CATSystem will send SMS to women to prompt return to the hospital. To protect confidentiality, the following steps will be taken: Study staff will be trained regarding the need to strictly protect confidentiality; this will also be reinforced with the clinic staff. Prior to starting the study, we will meet with clinic staff and peer counselors to identify any additional strategies that could be taken in that particular setting to help improve participant confidentiality. This includes strict adherence to protocols for the content of CATSystem text messages and procedures for those engaged in patient tracing in the community. Messages sent by the CATSystem were designed to protect patient confidentiality, by not referring to cervical cancer. Loss of confidentiality is also a risk for participants of the focus group discussions and surveys. While facilitators will emphasize the need for confidentiality amongst participants, confidentiality cannot be fully guaranteed in a focus group setting. This will be explained to participants.
4. **Economic risk:** The CATSystem will prompt patient retention in standard of care clinical services; however, will not financially support the provision of these services. In instances where women are prompted to return for services by the CATSystem – but would not have otherwise returned – they will be responsible for covering the costs of the services they receive.
5. **Potential benefit of participating in the study:** The potential for individual benefit from study participation exists, particularly among women enrolled in the intervention arm. In preliminary data, the CATSystem improved retention in cervical cancer screening and treatment. Early detection of

cervical cancer and early treatment can significantly improve prognosis and reduce costs later. Findings from this study will make an important contribution to cervical cancer services in Kenya and other comparable low resource countries and will contribute to the limited data regarding the implementation of eHealth strategies in this context. As Kenyan and global recommendations move toward eHealth and screen and treat strategies, it is critical to assess the performance and cost-effectiveness of these methods in resource-constrained settings. This data will provide evidence for Ministries of Health and other organizations to consider optimal mHealth strategies to meet the global cervical cancer goals.

